### Statistical analysis

Analysis will be conducted according to the intention-to-treat principle. In bivariable analysis, Pearson’s correlation will be used for continuous variables, Student’s *t*-test for dichotomous variables such as gender, and ANOVA for categorical variables such as the post-operative care regimen. Multivariate analyses will only be performed *post hoc* and are considered hypothesis-inducing as opposed to hypothesis-testing and will be ascribed as such.

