## Abstract

**Background:**

The optimal post-operative care regimen after surgically fixed Lauge Hansen supination exorotation injuries remains to be established. This study compares whether unprotected weight bearing as tolerated is superior to protected weight bearing and unprotected non-weight bearing in terms of functional outcome and safety.

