### Sample size and power

Our hypothesis is that ankle-specific disability assessed with the OMAS is less for unprotected weight bearing when compared to protected weight bearing and unprotected non-weight bearing. An *a priori* power analysis for superiority of treatment with unprotected weight bearing has been conducted for this hypothesis. To detect a clinically significant 7-point difference on the OMAS at 12 weeks follow-up between unprotected non-weight bearing and unprotected weight bearing with a standard deviation of 10, α = 0.05, β = 0.90, two-sided test (based on superiority of unprotected weight bearing), and a maximum loss to follow-up of 20%, a sample size of 75 patients per group is necessary. Therefore, a total of 225 patients are needed for this study.

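### The only test named for the regimens is a non-directional three-group ANOVA, which does not test the stated superiority of unprotected weight bearing over each comparator

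*Protocol article*

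**What the plan says.** Three parts of the protocol article bear on the primary comparison. UWB, PWB and NWB stand for unprotected weight bearing, protected weight bearing and unprotected non-weight bearing.

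- **Aim and hypothesis.** The abstract asks whether "unprotected weight bearing as tolerated is superior to protected weight bearing and unprotected non-weight bearing". Sample size and power states the hypothesis that "ankle-specific disability assessed with the OMAS is less for unprotected weight bearing when compared to protected weight bearing and unprotected non-weight bearing".
- **Power.** The same section sizes the trial for a "7-point difference on the OMAS at 12 weeks follow-up" "between unprotected non-weight bearing and unprotected weight bearing with a standard deviation of 10", with a two-sided alpha of 0.05, 90% power (printed as β = 0.90) and 20% loss. It arrives at 75 per group, 225 in all. PWB does not enter the calculation.
- **Analysis.** Statistical analysis lists bivariable methods by type of variable. Student's t is the "test for dichotomous variables such as gender", and the regimens fall under "ANOVA for categorical variables such as the post-operative care regimen". The section names no contrast between regimens. Multivariate analyses are post hoc and hypothesis-generating only.

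**The concern.** The hypothesis consists of two directed comparisons, UWB against each of two arms. The power statement covers one of them. The named test covers neither specifically: its null is that all three means are equal, and it rejects for any departure from that, including a difference between the two comparators or an inferior UWB arm.

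This goes beyond leaving detail to an analysis plan. The article names a test for the regimens, and that test does not answer the question the article poses. A significant F leaves open which arm is better than which, and so which finding counts as confirmation of the hypothesis. The question also reaches the interim analysis, because the DSMB section allows statistically significant and clinically relevant interim results to support early termination without saying which comparison is meant.

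**Working it through.** **Inputs.** Difference 7 points, SD 10, two-sided alpha 0.05, power 90%, loss 20%, 75 per group (Sample size and power); equal allocation (Randomization process). Evaluable per arm: 75 × 0.8 = 60. The patterns of means below are assumptions chosen to show how the test behaves.

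**1. The plan's own figure.** n = 2(z₀.₉₇₅ + z₀.₉₀)² SD²/Δ² = 2 × (1.960 + 1.282)² × 100/49 = 42.9, so 43 evaluable and 43/0.8 = 54 enrolled per group. The exact t-test gives 44 evaluable and 55 enrolled. The stated 75 does not follow from the stated inputs. That is a separate matter, and it errs on the large side. The checks below use 60 evaluable, which is what 75 enrolled provides.

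**2. Behaviour of the ANOVA.** Noncentrality λ = n Σ(μᵢ − μ̄)²/SD²; the critical value of F(2, 177) at 0.05 is 3.047.

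- One arm 7 points away from the other two: the mean of (0, 7, 7) is 4.667, so Σ = 21.78 + 5.44 + 5.44 = 32.67 and λ = 60 × 32.67/100 = 19.6. Power is 98.2%. By symmetry (0, 0, 7) gives the same λ whichever arm is the odd one out.
- Evenly spaced means (0, 3.5, 7): Σ = 24.5, λ = 14.7, power 93.6%, whichever arm lies in the middle.

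| True position (7 points unless stated) | F significant | UWB significantly better than both |
|---|---|---|
| UWB = PWB, NWB worse | 98% | about 2.5% |
| UWB = NWB, PWB better | 98% | 0% |
| UWB worse than both | 98% | 0% |
| UWB midway, NWB 3.5 below, PWB 3.5 above | 94% | 0% |
| UWB better than both | 98% | 94% |

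The first column is the noncentral F and the second is simulation, with each contrast at two-sided 0.05. The F-test cannot tell the last row from the first three. In the first row UWB really is 7 points better than NWB, so 98% there is power to detect a real difference; what is missing is superiority over PWB. In the second and third rows UWB is superior to neither comparator.

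**3. The two contrasts the hypothesis names.** Noncentrality = Δ/(SD√(2/n)) = 7/(10 × √(2/60)) = 3.834 on 118 degrees of freedom.

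- At two-sided 0.05 (critical value 1.980): power 96.7% per contrast.
- At two-sided 0.025 (critical value 2.270): power 94.0% per contrast.
- Both contrasts significant at 0.05 when UWB is 7 points above each: about 94%.
- If PWB lies halfway, so that UWB exceeds it by 3.5: both significant in about 47%.
- By the normal formula, 0.025 per contrast needs 51 evaluable, or 51/0.8 = 64 enrolled, per group. This is below 75.

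**4. Error rates when all three means are equal (simulation).**

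- Ungated pairwise tests at 0.05, any one rejection counting: 9.0% for the two UWB contrasts and about 12% for all three pairs.
- Both UWB contrasts required in favour of UWB: about 0.5%. If UWB equals PWB and both beat NWB by 7, the false claim of superiority to both is about 2.5%.
- Pairwise tests run only after a significant F: 5.0% for any of the three pairs.

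**The case against.** The strongest reply is that the Statistical analysis section is a short, generic list of methods by variable type in a condensed article, and that contrasts and multiplicity rules are commonly left to an analysis plan that is not shown. Much of this stands, and it rules out four stronger readings.

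- **That a significant ANOVA would be declared success.** A reader might infer this, but nothing in the article calls the ANOVA decisive or says that its significance proves UWB superior.
- **That the plan carries a 9.0% or 12% error rate.** Those figures apply only to ungated tests where any single win counts. The hypothesis, read literally, requires superiority to both comparators, and then no alpha split is needed. With exactly three groups, pairwise tests gated by a significant F hold 5%. Naming ANOVA does not by itself produce inflation.
- **That the primary time point is undefined.** The power analysis is stated to serve the hypothesis, and it fixes 12 weeks. Repeating this in the analysis section would help, but its absence there is not a fault in itself.
- **That one multiplicity rule is required.** Several are valid, and a fixed sequence starting with NWB would allow a confirmatory claim against NWB alone, which is less than the hypothesis states.

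The reply does not remove the mismatch. The article assigns a test to the regimens, assigns the t-test elsewhere, and leaves the PWB half of its hypothesis without a test or a place in the power calculation. The power statement implies a pairwise test for UWB versus NWB only.

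**Conclusion.** The point holds as a mismatch between the stated hypothesis and the one test named for it. A significant three-group ANOVA does not establish that UWB is superior to PWB and NWB: at 60 evaluable per arm and SD 10 it occurs in 98% of trials in which UWB merely equals PWB with NWB 7 points worse, and equally often when UWB equals NWB and only PWB is 7 points better.

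The figures assume normal outcomes with a common SD of 10, the full 20% loss and the patterns of means shown. The qualitative conclusion depends on none of these, because it follows from the null hypothesis of the F-test. The documents do not support saying that the trial will claim superiority from the F-test alone, or that its error rate is inflated. They leave the success rule open, and that is what needs settling.

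**What to change.** In Statistical analysis, name UWB versus NWB and UWB versus PWB on the 12-week OMAS as the two primary contrasts, each reported as a difference with a 95% CI. Make the three-group ANOVA and the PWB versus NWB comparison secondary.

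State the success rule before data are seen:

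- **Both must succeed**, as the hypothesis literally reads: test each contrast at two-sided 0.05 with no alpha split.
- **Either may count**: use an error-controlling rule such as a fixed sequence, Dunnett, Bonferroni (94% power per contrast at 0.025 for 7 points) or pairwise tests gated by the F-test.

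The cost is wording. With a 7-point difference and SD 10 for both contrasts, 75 per group is enough under either rule. The downside of requiring both is a lower chance of an overall positive result when the difference from PWB is smaller than 7 points: about 47% if it is 3.5 and UWB exceeds NWB by 7, against about 94% if UWB exceeds both by 7. With a fixed sequence, no confirmatory claim on the second contrast is possible if the first fails.

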## Methods and design

### Study design

This is a prospective multicenter randomized controlled trial involving six hospitals in the Netherlands. The study has been approved by the local Institutional Review Board under protocol number WOW-01/NL40835.100.12. This study compares three different post-operative care regimens after ankle surgery; all patients with a Lauge Hansen supination exorotation type 2, 3 or 4 ankle fractures requiring surgical treatment are eligible for inclusion.

After registration of the patient, an anonymous X-ray is sent to an expert panel consisting of six experienced orthopedic trauma surgeons. The fracture is classified according to the Lauge Hansen classification and advice on whether or not operative fixation is indicated is provided within 24 hours. A patient is eligible for inclusion when a majority of the expert panel agrees that operative fixation is necessary and the fracture type meets the inclusion criteria. When votes are split equally, the chairman (LL) is the tiebreaker. A flow chart of the study is shown in Figure 1.

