### Randomization process

Patients are randomized using computerized block randomization to either protected weight bearing, unprotected non-weight bearing, or unprotected weight bearing. The randomization is stratified by the participating hospitals. The blocks for randomization consist of 21 patients with the three post-operative care regimens equally represented in each block. Follow-up is by the intention-to-treat principle. Following surgical fixation, the treating surgeon logs into the private website where the patient is randomized to one of three post-operative care regimens.

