**Table 2 Tab2:** **Study assessments by time-point**

**Time point**	**Intake**	**2 weeks**	**6 weeks**	**12 weeks**	**6 months**	**1 year**
OMAS^a^	**X**		**X**	**X**	**X**	**X**
SF-36^b^	**X**			**X**		**X**
Wound inspection		**X**	**X**			
Calf circumference			**X**	**X**	**X**	**X**
Range of motion			**X**	**X**	**X**	**X**
Demographics	**X**					

^a^Olerud Molander Ankle Score.

^b^Short Form 36.

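### The regimen comparison is fixed as an unadjusted ANOVA, and adjustment for the stratifying hospital and for intake OMAS is allowed only post hoc

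*Protocol article*

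**What the plan says.** All references are to the protocol article.

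- **Statistical analysis.** Under bivariable analysis, the method that covers the treatment comparison is "ANOVA for categorical variables such as the post-operative care regimen". The next sentence deals with larger models: "Multivariate analyses will only be performed" post hoc, and they "are considered hypothesis-inducing as opposed to hypothesis-testing and will be ascribed as such".
- **Randomization process.** "The randomization is stratified by the participating hospitals". On blocking: "The blocks for randomization consist of 21 patients with the three post-operative care regimens equally represented in each block".
- **Study design.** The trial is a "prospective multicenter randomized controlled trial involving six hospitals in the Netherlands", so there are six strata.
- **Table 2** ("Study assessments by time-point"). The OMAS row is marked at intake, 6 weeks, 12 weeks, 6 months and 1 year.
- **Sample size and power.** The calculation is for a 7-point OMAS difference at 12 weeks with a standard deviation of 10, two-sided alpha of 0.05, and "a maximum loss to follow-up of 20" per cent. It gives 75 patients per group.
- **Primary outcome measures.** Between-group differences of 5 to 10 OMAS points are taken as clinically relevant.

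**The concern.** The design uses hospital to balance the arms, and the schedule collects a baseline value of the primary outcome. The analysis text then keeps both out of the confirmatory comparison. When allocation is balanced within hospital, differences between hospitals do not contribute to the true variance of the treatment contrast. An ANOVA without hospital still counts them in its residual, so its standard error is too large. Leaving out a baseline covariate that predicts outcome gives up precision that would cost no extra patients.

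This is a stated rule and not detail left for a later document. With the word *only*, an analysis plan that named an adjusted primary model would contradict the protocol. If the investigators later preferred the adjusted result, the protocol's own wording would class it as exploratory. What is at stake is the power to detect differences near the lower end of the trial's relevance range.

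**Working it through.** **1. The plan's own sample size**

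n per arm = 2 × (SD/δ)² × (z₀.₉₇₅ + z₀.₉₀)² = 2 × (10/7)² × (1.960 + 1.282)² ≈ 42.9, so 43. This reads the printed β = 0.90 as power. After 20% loss: 43/0.8 = 53.75, so 54. The stated 75 is not reproduced. That is a separate matter; the steps below take 75 as given, so 75 × 0.8 = 60 evaluable per arm.

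**2. Leaving out hospital**

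The documents give no hospital intraclass correlation (ICC), so 0.02 to 0.10 is assumed. With arms balanced within hospital, true SE = √(1 − ICC) × unadjusted SE. The true two-sided error of a nominal 0.05 test is 2 × [1 − Φ(1.96/√(1 − ICC))].

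| ICC (assumed) | Unadjusted SE ÷ true SE | True type I error |
|---|---|---|
| 0.02 | 1.010 | 0.048 |
| 0.05 | 1.026 | 0.044 |
| 0.10 | 1.054 | 0.039 |

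Adding hospital alone moves power for 5 points from 78.8% to 80.2% at ICC 0.05, and from 79.4% to 82.3% at ICC 0.10. These figures assume full balance within hospital. With 225/6 = 37.5 patients per hospital on average and blocks of 21, last blocks will often be incomplete, so the balance is approximate.

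**3. Leaving out intake OMAS**

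The correlation r between intake and 12-week OMAS is not in the documents; 0.3 and 0.5 are assumed. Adjustment multiplies residual variance by 1 − r²: 0.91 at r = 0.3 (9% lower) and 0.75 at r = 0.5 (25% lower). The residual SD becomes 9.54 or 8.66.

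Power = Φ(δ/SE − 1.96), with SE = SD × √(2/60):

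| r (assumed) | SE | Power, 7 points | Power, 5 points | Difference detectable with 90% power |
|---|---|---|---|---|
| 0 (unadjusted) | 1.826 | 97.0% | 78.2% | 5.92 |
| 0.3 | 1.742 | 98.0% | 81.9% | 5.65 |
| 0.5 | 1.581 | 99.3% | 88.5% | 5.13 |

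For example, unadjusted at 5 points: 5/1.826 − 1.96 = 0.78, and Φ(0.78) ≈ 0.78.

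**4. Both together, by simulation**

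Six hospitals, 60 per arm, 4,000 runs per setting, ICC 0.05, r = 0.5. Type I error was 0.044 unadjusted and 0.053 adjusted (Monte Carlo SE about 0.003). Power for 5 points was 78.9% unadjusted and 89.5% adjusted. This agrees with the formulas.

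**5. Cost in degrees of freedom**

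Five hospital terms and one covariate take the residual degrees of freedom from 180 − 3 = 177 to 171, which is negligible.

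**The case against.** **The unadjusted comparison is valid.** This stands. A comparison of randomised arms without covariates is unbiased, and leaving out hospital makes the test conservative. At the design difference of 7 points, adjustment raises power only from 97.0% to between 98.0% and 99.3%.

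**The gain rests on assumed inputs.** This also stands. Patients are recruited in the emergency room or before surgery, those with impaired mobility beforehand are excluded, and the article does not say whether intake OMAS describes the state before or after injury. Scores could cluster near the top or the bottom of the scale, and the gain would then be close to nil.

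**Multivariate might mean several outcomes.** In the strict sense the restriction would then not touch covariate adjustment. The contrast with bivariable in the same paragraph makes the multivariable reading much more likely. If the strict sense is meant, the wording still needs clearing up.

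**A reader might infer more than the text supports.**

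- *That a one-visit ANOVA makes this a completer analysis, in conflict with intention to treat.* The article says nothing about how missing OMAS values are handled. ANOVA can follow imputation, and such handling is commonly left to the full protocol or analysis plan. The 20% is a planning ceiling, not a forecast of missing 12-week scores.
- *That dropout would bias the contrast by a stated number of points.* Any such figure depends on how dropout is assumed to relate to recovery in each arm. The documents do not describe this.
- *That a repeated-measures model over all OMAS visits is required.* The powered contrast is at a single visit, and a single-visit analysis can include hospital and baseline.

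**Conclusion.** The point holds as one of efficiency. The article states a rule that excludes the stratification factor and the baseline value of the primary outcome from confirmatory use, and it gives no reason. The effect is a mildly conservative test (true type I error about 0.048 to 0.039 for an ICC of 0.02 to 0.10) and forgone precision (residual variance 9 to 25% lower with adjustment, for r of 0.3 to 0.5). It is of little consequence at 7 points. It is useful at 5 points, where power rises from 78% to 82 to 89%, and it would also help if the standard deviation exceeded 10. The sizes rest on an assumed ICC and correlation, on 60 evaluable patients per arm, and on near balance within hospitals. The direction for hospital does not depend on the exact ICC, whereas the gain from intake OMAS could be nil. The change is worth making because it is nearly free. It is not a flaw that would invalidate the trial's result.

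**What to change.** - Prespecify the primary 12-week OMAS comparison as an analysis of covariance with regimen, hospital and intake OMAS.
- Limit the post hoc, hypothesis-inducing sentence to models with other covariates.
- Report the unadjusted ANOVA as a sensitivity analysis.
- A repeated-measures model that uses the other OMAS visits is an option, not a required correction.

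The cost is a few lines of analysis text and a little programming. Hospital and intake OMAS are already recorded, and no extra patients or visits are needed. The Trial status section reports 73 of 225 patients enrolled, so at that stage the model can still be fixed before the outcome data are analysed.

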### Data and safety monitoring board (DSMB) and interim analysis

Participation in this trial does not elicit additional risks besides the standard complications of ankle surgery, such as wound infections, deep venous thrombosis, and hardware failure [12,13]. Although all three post-operative care regimens are independently investigated, unprotected weight bearing by unrestricted mobilization as tolerated has not yet been investigated in a randomized trial. Therefore, strict criteria for premature termination are implemented.

A DSMB has been established. An interim analysis will be conducted after every serious adverse event and after half of the target enrollment is reached. The DSMB consists of two independent physicians and one clinical epidemiologist. The members are not committed to this trial. The DSMB will provide advice that will be disclosed to the Institutional Review Board. The steering committee may terminate the study prematurely if advised by the DSMB. In addition, statistically significant, sufficiently powered, and clinically relevant results during interim analysis may be compelling to terminate the trial prematurely. For this trial, the following termination criteria have been established:10% Hardware failure percentage in any of the treatment groups [20,21]Wound infection percentage exceeding 20% in any of the treatment groups [14,21]

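### The plan allows early stopping for a significant efficacy result at interim analysis without stating a boundary or excluding looks triggered by serious adverse events, beside an unadjusted two-sided alpha of 0.05

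*Protocol article*

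**What the plan says.** The section on the DSMB and interim analysis sets the schedule: "An interim analysis will be conducted after every serious adverse event and after half of the target enrollment is reached". No maximum number of analyses is given. The section says that the steering committee may end the trial on DSMB advice, and then adds a further route: "statistically significant, sufficiently powered, and clinically relevant results during interim analysis may be compelling to terminate the trial prematurely". That sentence speaks of interim analysis in general. It neither names the halfway look nor leaves out the looks that follow an SAE.

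The only numerical termination criteria are for safety (hardware failure and wound infection). No p-value, boundary or spending rule is given for efficacy.

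The section on sample size plans for a "clinically significant 7-point difference on the OMAS at 12 weeks follow-up", "with a standard deviation of 10, α = 0.05, β = 0.90, two-sided test", and concludes that "a sample size of 75 patients per group is necessary" after allowing for 20% loss. Nothing there or under Statistical analysis adjusts alpha for interim testing. The section on the primary outcome gives a clinically relevant difference as a range of 5 to 10 OMAS points, not a single threshold.

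**The concern.** An interim analysis that can end the trial on a significant result is a second chance to reject the null hypothesis. Unless its threshold is set so that the two chances together cost 5%, the trial's false-positive rate exceeds the 5% used for the sample size. A trial stopped early on a significant result also tends to overstate the effect.

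Two features make this worse. The number of analyses depends on SAEs, so it is uncapped and unknown in advance. Their timing may also be related to treatment arm, which makes them a poor trigger for an efficacy test. The two remaining conditions, sufficient power and clinical relevance, could limit the damage, but the first is undefined and the second is a range.

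**Working it through.** **Inputs from the article.** Difference 7 points, SD 10, two-sided alpha 0.05, 20% loss, 75 per group, equal allocation. The printed β = 0.90 is read as power 0.90.

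**The plan's own sample size.** n = 2(1.960 + 1.282)² × 10² / 7² = 42.9, so 43 per group; 43/0.8 = 53.75, so 54. The stated 75 is not reproduced. That is a separate matter: extra patients raise power (75 × 0.8 = 60 evaluable per group gives about 97%) but do not control alpha. The plan's 75 is used below.

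**Sample at the looks.** Half of 225 is 112, or 37 per arm; 37 × 0.8 ≈ 30 evaluable. The final has 60 evaluable per arm. The information fraction is 30/60 = 0.5, so under the null the two z-statistics are bivariate normal with correlation √0.5 = 0.707.

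**Halfway look plus final, p<0.05 at each.**
Type I error = 1 − P(|Z1| < 1.96 and |Z2| < 1.96) = 0.083.

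**Adding a clinical-relevance gate at the interim.** The standard error of the difference with 30 per arm is 10√(2/30) = 2.58 points, so p<0.05 already needs 1.96 × 2.58 = 5.1 points.
- 5-point gate: 5/2.58 = 1.94, below 1.96, so it has no effect: 8.3%.
- 7-point gate: 7/2.58 = 2.71 replaces 1.96 at the interim: 5.3%.
- Sensitivity, no losses (37 of 75 per arm): the standard error is 10√(2/37) = 2.32, the gates become z = 2.15 and 3.01, and the error is 6.9% and 5.1%, against 8.3% ungated.

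**Adding SAE-triggered looks.** The article gives no SAE count, so this is an assumption. Simulation, 60 evaluable per arm at the end:

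| Looks (evaluable per arm) | No gate | 5-point gate | 7-point gate |
|---|---|---|---|
| 30, 60 | 8.3% | 8.3% | 5.3% |
| 15, 30, 45, 60 | 12.6% | 11.5% | 9.1% |
| 20, 30, 40, 60 | 11.9% | 11.0% | 7.0% |

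**What the power condition can do.** Two-sample t-test power at the halfway look:

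| True difference | 30 per arm | 37 per arm |
|---|---|---|
| 7 points | 76% | 84% |
| 8 points | 86% | 92% |
| 10 points | 97% | 99% |

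If the condition means at least 90% power for 7 points, looks count only from about 43 evaluable per arm. One look at 43 and a final at 60 still gives 7.5%. Adding a 5-point gate gives 5.6%, and a 7-point gate 5.0%.

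**Timing.** At the planned 79 patients a year, 79 × 12/52 ≈ 18 patients enrol in any 12 weeks. About 18 of the first 112 would thus lack the 12-week OMAS when the enrolment trigger is met. With only 20 to 25 per arm evaluable, the ungated two-look error is 8.8% to 8.6%, so this is a minor effect.

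**Candidate boundaries at half information.** Interim p<0.001 and final 0.05: overall 0.0502. O'Brien-Fleming-type spending, about 0.003 then 0.049: overall 0.0500.

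**The case against.** The article prints no interim p-value. It never says that 0.05 applies at each look, and boundaries often sit in an analysis plan or DSMB charter, neither of which is shown. This stands as a limit: the 8.3% is conditional on ordinary significance being used. It does not remove the point. The article goes beyond silence, because it states an efficacy stopping criterion in terms of significance and an open-ended schedule to which the criterion can apply.

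The SAE-triggered analyses may well be meant as safety reviews: the section opens with surgical risks, and all its numerical criteria concern safety. This is a fair reading, but the text does not say it. The looks are uncapped and event-driven (SAEs plus one), so describing them as unlimited efficacy tests would go too far.

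The stopping rule is a conjunction, so significance alone overstates the inflation. This also stands, and it is why gated figures are given. Only the strictest joint reading, at least 90% power and at least 7 points, brings the error back to about 5%, and the article does not state that reading.

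Finally, the figures count errors in both directions. False claims in favour of unprotected weight bearing are half of them: about 4.1% against a nominal 2.5% for halfway plus final.

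**Conclusion.** The concern holds in limited form. The article permits efficacy stopping on significance, gives no boundary, and does not exclude SAE-triggered looks, while alpha is an unadjusted two-sided 0.05. For the powered comparison, the one scheduled interim look brings the type I error to about 8.3% if ordinary significance is used, or about 5.3% with a 7-point gate. With four equally spaced looks it is about 9% to 13%. These figures assume independent increments, 30 and 60 evaluable per arm at halfway and final, and, for four looks, an assumed SAE count and spacing.

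A reader might infer three stronger claims that the document does not support:
- *That the 5% error rate has certainly been lost.* No interim p-value is printed, and an unseen charter may set one.
- *That the power condition cannot be met at halfway.* It is undefined. For 7 points power is below 90%, but for 10 points, still within the article's clinically relevant range, it is 97% to 99%. What can be said is that an undefined condition does not protect the error rate.
- *That the error is far higher because unprotected weight bearing is compared with two regimens.* Two unadjusted comparisons already give about 9% with no interim look. That is a separate multiplicity question.

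**What to change.** 1. State that reviews triggered by an SAE are safety-only, with no comparison of OMAS by arm.
2. Allow one efficacy look, when half of the 225 patients have their 12-week OMAS instead of when half are enrolled.
3. Give its boundary: p<0.001 at the interim and 0.05 at the end (overall 0.0502), or O'Brien-Fleming-type spending at about 0.003 then 0.049.
4. Replace the requirement of sufficient power with that boundary.

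The cost is wording in the protocol and DSMB charter. No extra patients are needed, and the safety termination criteria are unaffected. The article reports 73 patients enrolled, so the halfway look was still ahead and the rule could be set beforehand.

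The downside is that early efficacy stopping becomes harder. With a true difference of 7 points and 30 evaluable per arm, the expected interim z is 7/2.58 = 2.71. By normal approximation, the chance of crossing is about 77% at 1.96, about 40% at p<0.003 (z = 2.97) and about 28% at p<0.001 (z = 3.29).
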